## Abstract

**Background:**

This project aims to evaluate the effectiveness of an innovative educational intervention in enhancing clinical decision making related to the management of hypertension in general practice. The relatively low level of uptake of clinical practice guidelines by clinicians is widely recognised as a problem that impacts on clinical outcomes. This project addresses this problem with a focus on hypertension guidelines. Hypertension is the most frequently managed problem in general practice but evidence suggests that management of Hypertension in general practice is sub-optimal.

**Methods/design:**

This study will explore the effectiveness of an educational intervention named the ‘Guideline Enhancement Tool (GET)’. The intervention is designed to guide clinicians through a systematic process of considering key decision points related to the management of hypertension and provides a mechanism for clinicians to engage with the hypertension clinical guidelines.

The intervention will be administered within the Australian General Practice Training program, via one of the regional training providers. Two cohorts of trainees will participate as the intervention and delayed intervention groups.

This process is expected to improve clinicians’ engagement with the hypertension guidelines in particular, and enhance their clinical reasoning abilities in general. The effectiveness of the intervention in improving clinical reasoning will be evaluated using the ‘Script Concordance Test’.

**Discussion:**

The study design presented in this protocol aims to achieve two major outcomes. Firstly, the trial and evaluation of the educational intervention can lead to the development of a validated clinical education strategy that can be used in GP training to enhance the decision-making processes related to the management of hypertension. This has the potential to be adapted to other clinical conditions and training programs and can benefit clinicians in their clinical decision-making. Secondly, the study explores features that influence the effective use of clinical practice guidelines. The study thus addresses a significant problem in clinical education.

## Background

The relatively low levels of uptake of clinical practice guidelines is widely recognised in the literature as a practical problem impacting on clinical outcomes [1,2]. This study aims to evaluate the impact of a clinical education intervention designed to enhance the use of clinical practice guidelines and develop clinicians’ clinical reasoning abilities. The study focusses on hypertension guidelines and their use within general practice in Australia.

Hypertension is an important health problem in the Australian general practice setting. Data from the Australian Diabetes, Obesity and Lifestyle (AusDiab) study showed that 28.6% of adults aged 25 years or over had hypertension [3]. The data collected from the Bettering the Evaluation and Care of Health (BEACH) program between January 2009 and 2010 showed hypertension to be the most frequently managed problem in general practice, accounting for 5.7% of all managed problems [4].

Despite the high prevalence and importance of hypertension in the GP setting, there is evidence of a significant deficit in the treatment of hypertension. Data from the AusDiab study showed that only 45.8% of patients with hypertension are being treated [3]. A retrospective study that examined the care provided to 1154 adult Australians showed that of the 4700 clinical encounters involving the management of hypertension, patients received appropriate care only 72% of the time [5].

The reasons for this evidence-practice gap are multi-factorial: while drug-related and patient related factors play a role, health professional-related factors are very important [6,7]. The latter includes difficulties faced by GPs in making management decisions that accommodate patient differences and preferences [8].

This issue was further highlighted in a recent study involving focus groups of Australian GPs that found that the desire to provide comprehensive, holistic care that incorporates patient concerns and context into management decisions was an important factor that affected the management of hypertensive patients [6]. There is therefore a clear need to recognise and respond to the contextual factors that influence clinical decision-making, and to consider these contextual factors in developing and implementing clinical guidelines.

The proposed project aims to address this need through an innovative clinical educational intervention and evaluate its feasibility and effectiveness. The intervention is named the ‘Guideline Enhancement Tool’ (GET) and is designed to:Promote effective use of hypertension guidelines by General Practitioners.Develop clinicians’ decision-making processes related to the management of hypertension.Enable the consideration of contextual factors that influence clinical decisions, and encourage participants to make recommendations for tailoring the guidelines to better suit General Practice contexts.

The design of the GET was informed by previous research [9-11], which highlighted the factors that influence the incorporation of updated evidence to practice. The influences were explored from the perspectives of translational research, and can be framed within the theoretical bases of clinical reasoning [12], evidence-based-medicine [13], and the theory of reasoned action [14]. The clinical education strategy facilitates clinicians’ cognitive engagement with these influences to achieve more effective uptake of guidelines.

## Methods and design

### Study design

This is a non-randomised, delayed intervention study design. The study is not randomised since the educational intervention will be administered in groups and randomising groups will require unrealistic sample size. However, using repeated measures and a delayed intervention design provides an optimal solution without compromising the study quality. Such a design is preferable for evaluation of the educational intervention since all participants receive the intervention and the design enables measure of progress across and within groups, including control for possible (although unlikely) differences between groups at the starting time.

Clinicians participating in this study will be recruited from a population of general practice registrars who are undergoing GPTerm1 or GPTerm2 stages of training at GP Synergy (a major provider of general practice training in Australia), at two training sites. Participants from site A will be the ‘early intervention group’ while the group at site B will be the ‘delayed intervention group’. The two interventions will be identical and will differ only by the time of implementation. Participants will undergo evaluations of clinical reasoning (based on the Script Concordance Test (SCT) [15] upon commencement of project (Time Point 1: before the early intervention), immediately after the early intervention and before the delayed intervention starts (Time Point 2), and at the end of the delayed intervention (Time Point 3).

The impact of the intervention will be measured by comparing the progress each group makes (changes in SCT scores) over each intervention period.

### Sample size

Two systematic reviews suggest that the effect size on SCT between resident doctors and expert doctors ranged 0–3.2; typically around 1 and the effect of educational interventions such as Educational meetings/interactive educational sessions was d > 1 [16,17]. Based on those studies, we expect that the intervention will yield an effect size of d ≥ 1.0 measured by the differences in the SCT results between the intervention and the control groups between Time Point 1 and Time Point 2. A similar increase is expected for the delayed intervention group between Time Point 2 and Time Point 3. Therefore, a sample size of 34 clinicians (17 intervention & 17 control) will have 80% power to detect an effect size of d = 1 (one sd.) with an alpha of 0.05 (two sides) [18].

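### The 80% power and 5% error rate assume independent registrars, but GET is delivered in groups with one site per arm, so the powered contrast cannot separate GET from site-specific change

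*Protocol article*

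**What the plan says.** The Sample size section expects a standardised effect of at least 1, measured as "differences in the SCT results between the intervention and the control groups between Time Point 1 and Time Point 2". It concludes that "a sample size of 34 clinicians (17 intervention & 17 control) will have 80% power to detect an effect size of d = 1", "with an alpha of 0.05 (two sides"). It mentions no ICC, design effect or assumption of independence.

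The Study design section explains the lack of randomisation: "The study is not randomised since the educational intervention will be administered in groups and randomising groups will require unrealistic sample size". It makes site A the early group and site B the delayed group, and says that repeated measures with a delayed intervention "provides an optimal solution without compromising the study quality". The section on the educational intervention places GET in workshop-style training sessions, followed by an expert panel discussion.

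The Statistical analysis section compares SCT changes within individuals and across groups over both periods by ANOVA. It says this identifies the source of the change, and it takes p < .05 as showing that the intervention succeeded.

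**The concern.** The two sections pull against each other. Study design accepts that group delivery would raise the sample size if groups were randomised. Sample size then counts individuals as if they were not grouped. Dropping randomisation does not remove the correlation among registrars who train at the same site and take part in the same workshops and panel discussion.

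With one site per arm, the Time Point 1 to 2 comparison is a comparison of two sites. Change scores remove stable differences in level between them. They do not remove a difference in the rate of progress, for example from local teaching in the same months. Such a difference could give p < .05 and be reported as an effect of GET, and the Discussion looks forward to a validated education strategy on the strength of this study.

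**Working it through.** **Inputs from the protocol article.** 17 per arm, d = 1 (SD = 1), two-sided alpha 0.05 (Sample size); one site per arm and group delivery (Study design); individual-level ANOVA (Statistical analysis).

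**Assumed input.** The ICC of SCT change is not given. Values of 0.01, 0.05 and 0.10 are used as a range, with one cluster of 17 per arm.

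**Step 1: reproduce the stated figure.** Two-sample t-test with independent observations: 32 degrees of freedom, critical value 2.037, noncentrality √(17/2) = 2.915. Power is 80.7% with 17 per arm and 78.1% with 16. So 17 is the smallest number per arm that reaches 80%, and the calculation is the individual-level one.

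**Step 2: true error rate of the planned test.** With one cluster of m = 17 per arm, the design effect is DE = 1 + 16 × ICC. The test estimates its variance within site, so the true variance of the difference exceeds the estimated one by the factor DE/(1 − ICC). The true two-sided error rate is P(|t32| > 2.037/√[DE/(1 − ICC)]).

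**Step 3: rejection rate of the same test at d = 1.** The threshold is that of step 2, with noncentrality 2.915/√DE.

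| Assumed ICC | DE | DE/(1 − ICC) | Effective threshold | True error rate | Noncentrality at d = 1 | Rejection rate at d = 1 |
|---|---|---|---|---|---|---|
| 0 | 1.00 | 1.00 | 2.037 | 5% | 2.915 | 81% |
| 0.01 | 1.16 | 1.172 | 1.882 | 6.9% | 2.707 | 79% |
| 0.05 | 1.80 | 1.895 | 1.480 | 14.9% | 2.173 | 76% |
| 0.10 | 2.60 | 2.889 | 1.198 | 24.0% | 1.808 | 73% |

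Simulation of the unadjusted t-test agrees (14.9% and 24.0% error at ICC 0.05 and 0.10).

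**Step 4: effective sample size, for comparison only.** 17/DE gives 14.7, 9.4 and 6.5 per arm. Noncentral-t power at d = 1 is then 74%, 54% and 38% (77%, 58% and 44% by a normal approximation). These figures belong to a test that knows the ICC and adjusts for it. With one site per arm there are no between-site degrees of freedom, so this study cannot run that test.

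**Step 5: a contrast within site B.** Site B's change from Time Point 2 to 3 minus its own change from Time Point 1 to 2 is T3 − 2·T2 + T1. If the three scores have equal variance σ² and equal correlation ρ, a single change has variance 2σ²(1 − ρ) and this contrast has variance 6σ²(1 − ρ), so its SD is √3 times larger. For an effect of one change-score SD and n = 17, the noncentrality is √17/√3 = 2.38 on 16 degrees of freedom (critical value 2.120), and power is about 61%.

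**The case against.** The strongest reply is that the design already answers much of this. The article openly declares a non-randomised two-site study and gives a practical reason. Both sites receive GET, both come from one training provider and the same training stages, and changes are compared within and across groups in both periods. Change scores remove fixed differences between sites, and site B's treated period is a partial replication within one site.

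This stands, and it limits the point. A reader might infer that site and intervention are confounded throughout the study. The documents do not support that: the two coincide only in the Time Point 1 to 2 contrast. That contrast, however, is the one the study is sized on. From Time Point 2 to 3 the comparison site has already been treated, so the second period is not a clean repeat of the first.

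A reader might also infer that power collapses to 38%. That figure mixes two tests. It comes from an ICC-adjusted analysis that is neither planned nor possible here; the planned test still rejects in 73% or more of trials at d = 1 over the assumed range.

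Finally, the number of sessions per site is not stated. Smaller sessions would reduce correlation from that source: with 6 registrars per session and ICC 0.05, the design effect is 1 + 5 × 0.05 = 1.25 instead of 1.80. Site would still coincide with arm.

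**Conclusion.** Wrong as written. The arithmetic behind 34 registrars is correct, but 80% power and 5% error hold only if SCT change has no site or session variance. The article's own account of group delivery makes that doubtful, and one site per arm makes it uncheckable. A later analysis plan could not supply the missing degrees of freedom.

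The consequence is mainly false attribution: a true error rate of about 7% to 15% at ICC 0.01 to 0.05, and 24% at 0.10. These sizes rest on assumed ICCs and one cluster of 17 per arm; the direction does not depend on the value chosen, since any positive ICC raises the error rate. The claim that quality is not compromised, and the use of p < .05 on the between-site contrast alone as proof of success, are not supported. It does not follow that the design is uninformative or that more sites are required.

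**What to change.** 1. **Sample size.** Restate the figure along these lines: *80% power and 5% two-sided error assuming no site- or session-level variance in SCT change; with one site per arm this cannot be checked, and an ICC of 0.01 to 0.05 would raise the error rate to about 7% to 15%.* Do not print an ICC-adjusted power, because no such test can be run.
2. **Study design and Statistical analysis.** Delete the claim that the design "provides an optimal solution without compromising the study quality". State that the Time Point 1 to 2 between-site contrast cannot by itself separate GET from site-specific change, and do not treat p < .05 on that contrast alone as demonstrating success.
3. **Supporting contrast.** Pre-specify site B's Time Point 2 to 3 change minus its own Time Point 1 to 2 change. Report its estimate and confidence interval beside the between-site contrast. Note its lower power (about 61% under the assumptions in step 5) and its exposure to period and retest effects. Interpret the two together, without requiring them to agree in size.

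**Cost.** Changes of wording and one extra contrast from data already planned. The stated operating characteristics and the strength of the conclusion become less favourable.

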### Statistical analysis

The main analyses in this study will employ Analysis of Variance (ANOVA). (a) Factorial ANOVA will be used to compare the two groups at Time Point 1 and identify possible differences on SCT scores across groups; (b) One-way repeated measure ANOVA will be used to measure the impact of the intervention by comparing differences in SCT scores within individuals and across groups between Time Point 1–2 and between Time Point 2–3. This analysis is appropriate as it allows identifying the source for the change in the SCT scores (intervention, initial level of competence or errors [20], and testing the hypothesis that the change in the SCT was made by the intervention. We set up a significance level of p < .05 to demonstrate that the intervention was successful.

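### The sample of 34 has no slack for missing scores, and the repeated-measures ANOVA discards partial records; a mixed model on all available scores would keep them

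*Protocol article*

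**What the plan says.** The Sample size section of the protocol article states that "a sample size of 34 clinicians (17 intervention & 17 control) will have 80% power" for a standardised effect of 1, tested two-sided at the 5% level. The contrast behind this figure is the "differences in the SCT results between the intervention and the control groups between Time Point 1 and Time Point 2". The section adds that a similar gain is expected in the delayed group over Time Points 2 to 3. It does not say whether 34 counts registrars recruited or registrars with scores.

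Under Study design, each registrar sits the Script Concordance Test (SCT) three times: before the early intervention, between the two interventions, and "at the end of the delayed intervention (Time Point 3").

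The Statistical analysis section says "The main analyses in this study will employ Analysis of Variance (ANOVA"). The effect of the intervention is to come from a repeated-measures ANOVA "comparing differences in SCT scores within individuals and across groups between Time Point 1–2 and between Time Point 2–3". The section gives no rule for a registrar with a missing score.

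**The concern.** Two choices fixed in the article fit poorly together. The sample size is the minimum for the stated power, so any lost score on the powered contrast costs power that the plan cannot spare. The named method, in its classical form, works on complete records: a registrar who lacks one score the model needs contributes nothing, even where the other scores exist.

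Two things are at stake. The first is precision, since a few absences matter with 17 per arm. The second is bias. If weaker or less engaged registrars are the ones who miss a sitting, the complete records no longer represent the group. The groups are not randomised and sit at two different sites, so selective absence would add to any comparability problem already present. The early group must also return for Time Point 3 after its own workshop is over, which is a plausible place for absence to differ between groups.

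**Working it through.** **Inputs from the Sample size section:** 17 per arm, d = 1, alpha 0.05 two-sided, stated power 80%, contrast over Time Points 1 to 2. **Not given:** a rate of missed sittings, the SD that defines d, and the correlation between sittings. Each value used for these below is an assumption.

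**Step 1. Reproduce the stated power.** For a two-sample t-test, df = n1 + n2 − 2 and the noncentrality is d / √(1/n1 + 1/n2). With 17 per arm, df = 32, the noncentrality is 1 / √(2/17) = 2.915 and the critical t is 2.037. Power is 80.7%, so the stated 80% is reproduced.

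**Step 2. Fewer scored registrars, same formula.**

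| Scored per arm | Noncentrality | Power |
|---|---|---|
| 17 and 17 | 2.915 | 80.7% |
| 17 and 16 | 2.871 | 79.4% |
| 16 and 16 | 2.828 | 78.1% |
| 15 and 15 | 2.739 | 75.3% |
| 14 and 14 | 2.646 | 72.1% |

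Seventeen is therefore the smallest equal-arm size that reaches 80%. The normal approximation is kinder: it needs 16 per arm (80.7%) and gives 83.0% at 17. The article's 17 matches the t-test.

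**Step 3. Which SD defines d.** Step 2 takes d in SDs of the quantity analysed. If d is instead in SDs of a single SCT score and the change is analysed, the SD of the change is √(2(1 − r)), where r is the correlation between sittings, and the effective d is 1 / √(2(1 − r)). With 16 per arm, power is 63.8% at r = 0.3, 78.1% at r = 0.5 and 94.2% at r = 0.7. The table in Step 2 thus also applies under this second reading when r = 0.5.

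**Step 4. What a mixed model recovers.** Suppose 17 per arm are scored at Time Point 1 and 15 of them at Time Point 2, with r = 0.5 and a score SD of 1. The variance of the estimated mean change in one arm is:

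- complete records only: 2(1 − 0.5)/15 = 0.0667, that is, 15 registrars' worth of information;
- mixed model on all scores: (1 − 0.5²)/15 + (1 − 0.5)²/17 = 0.0500 + 0.0147 = 0.0647, that is, 1/0.0647 = 15.5 registrars' worth.

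The standard error of the group difference is √(2 × 0.0647) = 0.360. With 28 to 32 degrees of freedom, power is 76.5% to 76.9%, against 75.3% for complete records. The gain is between 1 and 2 percentage points, and power stays below 80%.

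**Step 5. Which sittings matter.** The powered contrast uses Time Points 1 and 2 only. If the two intervals are analysed separately, a registrar who misses only Time Point 3 stays in that contrast. If one model is fitted to all three sittings with complete records only, the same registrar drops out of it. The article does not say which is meant.

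**The case against.** No figure in the article is wrong: 34 scored registrars do give 80% power, and the section expects d of at least 1, so d = 1 is the floor of its planning range. A reader might infer that power is overstated. That would follow only if 34 were the number recruited, which the article does not say, and only at an attendance rate it does not give. For the same reason nothing supports saying that the power cannot be met at any realistic attendance. One loss per arm costs 1.9 points against the stated 80%, and by the normal approximation costs nothing against it.

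A reader might also infer that the plan itself orders incomplete registrars to be dropped. It does not. Deletion is a property of the classical method named, and a missing-data rule may stand in a fuller document. A condensed article may likewise leave an attrition allowance to that document, so its absence alone is not a finding. Nor does every missed sitting reduce the stated power, because Time Point 3 is outside the powered contrast.

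The remedy has limits too. It does not bring power back to 80% when Time Point 2 scores are missing. Over three time points it is not always the same test as the ANOVA, because the univariate ANOVA assumes sphericity and a model with unstructured covariance does not.

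All of this stands. What remains is that the article fixes a method that wastes partial records in a small, non-randomised study with three sittings, when a method that keeps them is available at almost no cost.

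**Conclusion.** The point holds as an improvement to the analysis and a clarification of the power statement, not as an error in the sample size. The stated 80% is correct for 34 registrars with usable scores at Time Points 1 and 2, with no slack by the t-test: 78.1% with 16 per arm and 75.3% with 15. These figures take d in SDs of the analysed difference, or r = 0.5 if d is in single-score SDs.

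The precision gained from a mixed model on the Time Point 1 to 2 contrast is modest, about 77% against 75.3% in the assumed case of 15 of 17 per arm scored at Time Point 2. The larger reason for the change is protection against selective absence. That protection rests on scores being missing at random given the scores observed, and the size of the bias avoided cannot be worked out from the article.

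**What to change.** 1. In Statistical analysis, replace the repeated-measures ANOVA with a linear mixed model for SCT score with group, time and group by time as fixed effects and within-participant correlation over Time Points 1 to 3 (a participant random effect or an unstructured covariance), fitted to all available scores. Take the Time Point 1 to 2 and Time Point 2 to 3 group contrasts from this model. Say that it relies on missing at random.

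2. In Sample size, tie the figure to scored registrars, for example: *34 registrars (17 per group) scored at Time Points 1 and 2 give 80% power at d = 1; with 15 per group, power is about 75%.* State whether 34 is the number recruited or evaluable, and which SD defines d.

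The cost is a change of wording and a slightly less favourable power statement. No extra recruitment or data collection is needed. The change does not remove the loss of power from missing Time Point 2 scores; it only makes that loss visible.
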